# Effect of virtual reality-integrated mindfulness-based cognitive therapy on pain and psychological symptoms in chronic non-specific low back pain: protocol for a randomized controlled trial

**DOI:** 10.3389/fdgth.2026.1902063

**Published:** 2026-07-31

**Keywords:** back pain bothersomeness, chronic non-specific low back pain, mindfulness-based cognitive therapy, oswestry disability index, virtual reality

## Abstract

**Background:**

Chronic non-specific low back pain (CNLBP) is a common condition associated with persistent pain, functional limitation, reduced quality of life, and substantial healthcare and socioeconomic burden. Mindfulness-based cognitive therapy (MBCT) has been increasingly used in chronic pain management and may provide a promising therapeutic approach for CNLBP. The emergence of virtual reality (VR) further provides an immersive, standardized, and accessible platform for delivering MBCT. This study aims to evaluate the effects and safety of a CNLBP-specific VR-integrated MBCT intervention in patients with CNLBP.

**Methods:**

This multi-center, prospective, parallel-group, open-label randomized controlled trial will recruit 214 patients with CNLBP from the pain clinics of three hospitals. Participants will be randomly assigned in a 1:1 ratio to either an 8-week VR-MBCT group consisting of weekly in-clinic VR sessions supplemented by structured audio-guided home practice, or a usual care control group receiving usual care alone, such as pharmacotherapy and physical therapy, using stratified block randomization according to study center and age (≥60 years or <60 years), with block sizes of 2 and 4. The primary outcomes are the proportions of patients achieving at least a 30% improvement from baseline in functional disability, assessed by the Oswestry Disability Index (ODI), and in self-reported back pain bothersomeness, assessed on a 0–10 scale, at week 8. Secondary outcomes include pain intensity, anxiety, depression, sleep quality, kinesiophobia, pain catastrophizing, work productivity, system usability, and use of concomitant treatments. Safety outcomes will include VR-related adverse events, such as vertigo, vomiting and nausea, headache and falls. Assessments will be conducted at baseline, week 4, week 8, and week 26. Data will be analyzed according to the intention-to-treat principle using generalized estimating equations (GEEs).

**Discussion:**

This study aims to provide preliminary evidence regarding the efficacy and safety of VR-integrated MBCT as an adjunct to usual care in patients with CNLBP.

**Clinical Trial Registration:**

https://clinicaltrials.gov/ct2/show/NCT07589790, identifier NCT07589790.

## Introduction

1

Chronic non-specific low back pain (CNLBP) is a common musculoskeletal condition associated with persistent pain, functional limitation, reduced quality of life, and substantial healthcare and socioeconomic burden (1–4). Unlike low back pain caused by specific spinal pathology, CNLBP lacks a clearly identifiable structural cause (5). Conventional treatments, including pharmacotherapy and physical therapy, often focus on peripheral nociception and physical impairment, but may insufficiently address the cognitive, emotional, and behavioral dimensions of pain (6, 7). This may partly explain why many patients continue to experience persistent symptoms and functional disability despite treatment (8). Moreover, abnormal imaging findings do not necessarily correlate with pain severity (9, 10), suggesting that CNLBP can not be fully explained or managed through structural or pharmacological approaches alone (11).

Modern pain science increasingly emphasizes the biopsychosocial model, in which biological, psychological, and social factors jointly contribute to the development and persistence of chronic pain (12). Psychological factors such as pain catastrophizing, fear-avoidance beliefs, anxiety, and depression are closely involved in the maintenance of CNLBP (12–14). Accordingly, psychological interventions, including cognitive behavioral therapy (CBT) and mindfulness-based stress reduction (MBSR), have been used in chronic pain management and have shown beneficial effects in reducing pain and improving related outcomes (15–17). However, some patients obtain limited benefit from these approaches (18, 19), and their implementation may be constrained by therapist availability, time requirements, and patient adherence (20).

Mindfulness-based cognitive therapy (MBCT) integrates elements of CBT and mindfulness-based approaches, helping patients relate differently to pain-related thoughts, emotions, and bodily sensations through awareness and acceptance (21). Evidence for mindfulness-based interventions in chronic pain is promising but not conclusive. Recent reviews suggest potential benefits for pain and psychological symptoms, although the certainty of evidence varies across outcomes and is limited by small samples, intervention heterogeneity, and risk of bias (19, 22). Evidence specific to MBCT is more limited, with a meta-analysis reporting improvements in depressive symptoms but no clear effects on pain intensity or pain interference (23). Nevertheless, emerging studies suggest potential benefits for functional outcomes in chronic pain conditions (24–27). However, conventional MBCT usually requires experienced therapists and repeated face-to-face sessions, which may limit its accessibility in routine clinical settings (27).

Virtual reality (VR) has increasingly been used to deliver psychological and behavioral interventions for chronic back pain. In patients with chronic low back pain, home-based VR programs combining pain neuroscience education, cognitive-behavioral strategies, breathing, relaxation, and brief mindfulness exercises have improved pain intensity and pain interference (28). VR neuroscience-based therapy incorporating body awareness, attentional and emotional training, and pain reappraisal has also shown beneficial effects in patients with chronic back pain (29). A recent meta-analysis of 20 randomized trials found that VR-based interventions improved pain, pain-related fear, and disability in chronic low back pain (30). However, the authors of the meta-analysis noted that benefits driven by distraction within the virtual environment may diminish once patients return to daily life, highlighting the need for transferable psychological skills beyond the VR setting. Moreover, most existing VR-based pain interventions—including the FDA-authorized RelieVRx™—have been designed around a multi-modal “skills kit” model that integrates mindfulness exercises within broader cognitive-behavioral or relaxation frameworks rather than grounding the entire curriculum in a structured, MBCT-driven therapeutic protocol (31). While these approaches have demonstrated short-term efficacy, they do not systematically train patients to fundamentally transform their relationship with pain through sustained, progressive practice.

Integrating VR with MBCT may therefore provide a scalable platform for delivering these principles through immersive experiential learning, where abstract concepts such as bodily awareness and cognitive defusion can be concretized in interactive virtual environments. A recent study reported the feasibility and acceptability of VR-MBCT in patients with depression (32). However, VR-MBCT protocols specifically designed for chronic non-specific low back pain (CNLBP) remain underdeveloped, and high-quality randomized controlled evidence regarding their efficacy and safety is still lacking. Our present intervention addresses this gap: the content and progression of the entire 8-week program are based on MBCT, with weekly sessions progressing from attentional grounding to recognizing habitual reactions, decentering, and practicing mindful movement adapted for CNLBP. In this protocol, VR serves as an integrated delivery platform that guides and reinforces these specific MBCT practices rather than functioning primarily as a distraction tool or a repository of isolated coping techniques.

This study aims to evaluate the efficacy and safety of a CNLBP-specific VR-MBCT intervention for patients with CNLBP. We hypothesize that, compared with usual care, an 8-week VR-MBCT program will result in greater improvement in functional disability and pain bothersomeness.

## Methods

2

This study protocol was approved by the Ethics Committee of the First Affiliated Hospital of Soochow University (Approval No. 2026306, Approval Date: March 19, 2026). Written informed consent will be obtained from all participants prior to enrollment. All study procedures will be conducted in accordance with the Declaration of Helsinki and Good Clinical Practice (GCP) guidelines. Additionally, this protocol was developed in accordance with the SPIRIT (Standard Protocol Items: Recommendations for Interventional Trials) guidelines, as outlined in Supplementary File S1.

File 1. SPIRIT 2013 Checklist: Recommended items to address in a clinical trial protocol and related documents.

### Study design and patients

2.1

This study is a multi-center, prospective, randomized, parallel-group, open-label clinical trial designed to evaluate the efficacy and safety of VR-integrated MBCT in patients with CNLBP. The trial will be conducted at the First Affiliated Hospital of Soochow University, Suzhou Xiangcheng People's Hospital, and The Fourth Affiliated Hospital of Soochow University, enrolling a total of 214 patients. Recruitment and follow-up are scheduled to take place between May 2026 and January 2027. Data collection is expected to be completed by February 2027, and data analysis by March 2027. Study flow diagram showing the enrollment and randomization process is shown in Figure 1.

**Figure 1 F1:**
[figure not shown]
Study ﬂow diagram showing the enrollment and randomization process.

### Inclusion criteria

2.2

Patients who meet the following criteria will be included:
Diagnosed with CNLBP according to standard criteria (3), with pain duration ≥3 months.Aged 20–70 years (inclusive).Average self-reported back pain bothersomeness ≥4(scale, 0–10) in the past week.Provided informed consent and family members will be informed of the study as support persons.

### Exclusion criteria

2.3

The exclusion criteria include:
Coexisting pain conditions that may interfere with the assessment of CNLBP.Severe neurological or psychiatric disorders (e.g., unstable epilepsy, psychosis, dementia).Severe psychiatric comorbidities (e.g., active suicidal ideation, severe depression requiring antidepressant medication).History of substance abuse (including alcohol or drugs) in the past year.History of accidents or injuries related to back pain in the past year.Severe visual impairment, vertigo, or history of VR-induced motion sickness precluding safe VR use.Inability to communicate effectively to express subjective feelings.

### Primary outcome

2.4

The primary outcome is defined as the proportions of patients achieving at least a 30% improvement from baseline in functional disability and self-reported back pain bothersomeness at week 8. Functional disability will be assessed using the Oswestry Disability Index (ODI), and back pain bothersomeness will be measured on a 0–10 scale (0 indicates not at all bothersome; 10 indicates extremely bothersome. The ODI is a validated instrument for assessing disability in patients with chronic low back pain, with or without radiculopathy (33). It consists of 10 items scored on a 6-point Likert scale, with total scores ranging from 0 to 100%, where higher scores indicate greater disability (34). Back pain bothersomeness reflects the overall subjective burden of pain and is consistent with the multidimensional perspective of the biopsychosocial model. A treatment responder is defined as a patient achieving at least a 30% improvement from baseline at the primary 8-week endpoint. This responder definition was selected based on the international consensus proposed by Ostelo et al., which recommended a 30% improvement from baseline as a practical threshold for identifying clinically meaningful change in individual patients (35). This threshold has subsequently been widely adopted in low back pain research (36, 37) and has demonstrated validity in predicting patient satisfaction in large real-world validation studies (38). The co-primary composite endpoint requires concurrent improvement in both disability and pain bothersomeness, providing a stringent and clinically interpretable definition of treatment response.

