### Sample size calculation

2.10

The sample size was calculated based on the co-primary outcomes: response rates for functional disability and self-reported back pain bothersomeness. The primary outcome is defined as the proportion of patients achieving clinically meaningful improvement, defined as at least a 30% improvement from baseline, in both functional disability and back pain bothersomeness after 8 weeks of intervention. Based on previous studies of mind-body interventions for chronic low back pain (15, 39), we assumed that 35% of participants in the usual care group and 55% of participants in the VR-MBCT group would achieve clinically meaningful improvement, corresponding to an absolute between-group difference of 20 percentage points. With a two-sided significance level of 0.05, 80% power, and a 1:1 allocation ratio, 97 patients per group were required for each co-primary outcome. This sample size was considered sufficient to provide adequate power for both co-primary outcomes; the study will be considered positive only if both outcomes reach statistical significance. Allowing for a 10% dropout rate, the total sample size was set at 214 patients, with 107 patients in each group. Sample size calculations were performed using PASS software, version 15.0 (NCSS, LLC, USA).

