### Statistical analysis

2.11

All analyses will follow a prespecified statistical analysis plan and will be conducted according to the intention-to-treat principle, whereby participants will be analyzed according to their randomized group assignment regardless of intervention adherence. Continuous variables will be summarized as means with standard deviations or medians with interquartile ranges, as appropriate, while categorical variables will be summarized as frequencies and percentages. All statistical tests will be two-sided, and statistical significance will be defined as a *P* value <0.05.

For the co-primary outcomes, separate regression models will be fitted for functional disability and self-reported back pain bothersomeness. Outcomes from all follow-up time points (weeks 4, 8, and 26) will be analyzed simultaneously using generalized estimating equations (GEEs) to account for within-participant correlations over time. Because treatment effects may vary across follow-up periods, models will include fixed effects for treatment group, time point, and treatment-by-time interaction terms. Baseline values of the corresponding outcome measures, study center, age group (≥60 years vs. <60 years), sex, pain duration, and other clinically relevant baseline covariates associated with outcomes or missingness will be included as adjustment variables.

The co-primary outcomes are binary responder outcomes, defined as at least a 30% improvement from baseline. Therefore, modified Poisson regression models with a log-link function and robust sandwich variance estimators will be used within the GEE framework to estimate relative risks and corresponding 95% confidence intervals. The primary endpoint will be evaluated at week 8. The study will be considered positive only if both co-primary outcomes reach statistical significance at the primary endpoint.

Continuous secondary outcomes, including pain intensity, psychological scores, sleep quality, physical activity, fear-avoidance beliefs, pain catastrophizing, and work productivity, will be analyzed using linear GEE models or linear mixed-effects models, as appropriate according to outcome distributions and covariance structures. Secondary outcomes assessed only at selected time points will be analyzed using models including the corresponding follow-up assessments.

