## Discussion

3

This multi-center, prospective, randomized, parallel-group, open-label clinical trial involves patients with chronic non-specific low back pain and aims to evaluate the efficacy and safety of VR-integrated mindfulness-based cognitive therapy as an adjunctive intervention. The intervention combines weekly facilitator-guided, in-clinic VR-MBCT sessions with structured audio-guided mindfulness practice at home, allowing participants to reinforce the skills introduced during the VR sessions in their daily lives. The primary objective is to determine whether an 8-week VR-MBCT program improves treatment response, defined as at least a 30% improvement from baseline in both functional disability and self-reported back pain bothersomeness at week 8. Secondary objectives include evaluating changes in pain intensity, psychological symptoms, sleep quality, physical activity, fear-avoidance beliefs, pain catastrophizing, work productivity, use of concomitant treatments, system usability, patient satisfaction, and safety outcomes, including dizziness, headache, nausea, vomiting and falls. This study will be conducted and reported in accordance with the SPIRIT guidelines.

This study seeks to overcome some limitations of conventional therapy by integrating VR with MBCT. VR technology can provide a highly standardized and immersive training environment, thereby ensuring consistency across intervention sessions. In addition, visualization and gamified elements may help patients better understand and practice relatively abstract MBCT concepts. This immersive and interactive format may support engagement by making practices such as bodily awareness and decentering more concrete. Attendance at the weekly in-clinic sessions and completion of prescribed home-based audio practice will be recorded to evaluate adherence to the present intervention. This approach may support engagement, in contrast to traditional models that rely heavily on therapist expertise and patient self-motivation (32, 40).

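### The primary endpoint is defined as a both-domains responder, but the analysis and success rule use two separate responder endpoints

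*Protocol article*

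**What the plan says.** Two forms of the primary endpoint stand in the protocol article.

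**One response per patient, requiring both measures**
- Section 2.4 (Primary outcome), last sentence: "The co-primary composite endpoint requires concurrent improvement in both disability and pain bothersomeness".
- Section 2.10 (Sample size calculation), in the singular: "The primary outcome is defined as the proportion of patients achieving clinically meaningful improvement", continued as "in both functional disability and back pain bothersomeness after 8 weeks of intervention".
- Discussion, first paragraph, where the primary objective concerns treatment response, "defined as at least a 30% improvement from baseline in both functional disability and self-reported back pain bothersomeness at week 8".

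**Two separate responder endpoints**
- Abstract, Methods, in the plural: "The primary outcomes are the proportions of patients achieving at least a 30% improvement from baseline in functional disability", with bothersomeness named alongside as the second measure.
- Section 2.10: "97 patients per group were required for each co-primary outcome".
- Section 2.11 (Statistical analysis): "For the co-primary outcomes, separate regression models will be fitted for functional disability and self-reported back pain bothersomeness".

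Sections 2.4 and 2.10 each contain both forms: 2.4 opens with plural proportions and closes with the composite, and 2.10 moves from the composite definition to a per-outcome sample size. Sections 2.10 and 2.11 both say that the study is positive only if both co-primary outcomes are significant, and 2.11 places that test at week 8. No section gives a model or test for the composite.

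**The concern.** The two forms ask different questions. The composite counts patients who improve by at least 30% on both the ODI and bothersomeness, and compares that single proportion once. The co-primary form compares each measure across all patients and needs two significant results. Response rates, power and the meaning of a positive trial all differ. The two are certain to agree only if every patient who responds on one measure also responds on the other.

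Three things are at stake. First, a composite result could be presented as meeting the stated objective after the two-test rule had failed; in an open-label trial with patient-reported primary outcomes, that room should be closed in advance. Second, the composite can reach significance when only one domain responds to treatment, which the requirement for two significant tests is there to prevent. Third, the 35% and 55% rates directly follow the both-measures definition in 2.10 and are then applied to each outcome, so they cannot be tied to one endpoint.

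**Working it through.** **Inputs.** From 2.10: 35% versus 55% responders, two-sided 0.05, 80% power, 1:1 allocation, 97 per group, 10% dropout, 214 in total. Assumed: the within-arm correlation (phi) between the two responder indicators, which the article does not give; it is varied from 0 to 1. Simple pooled z-tests stand in for the adjusted GEE models.

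**The plan's own figure.** For one binary endpoint,

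n = [1.960·√(2·0.45·0.55) + 0.842·√(0.35·0.65 + 0.55·0.45)]² / 0.20² = (1.379 + 0.580)² / 0.04 ≈ 96 per group.

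The stated 97 is reproduced within rounding and gives 80.4% power. Dropout: 96/0.9 or 97×1.1 both round up to 107 per group, 214 in total. The sample size therefore gives 80% power for one test.

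**Composite rates if 35%/55% holds on each endpoint.** The rate on both measures is p² + phi·p(1−p). At phi 0.5:
- control: 0.1225 + 0.5·0.2275 = 23.6%
- VR-MBCT: 0.3025 + 0.5·0.2475 = 42.6%

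**How often the verdicts differ.** 200,000 simulated trials per setting, 97 per arm:

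| phi | Composite positive | Both tests positive | Verdicts differ | Composite only | Two tests only |
|---|---|---|---|---|---|
| 0 | 88% | 65% | 27% | 24.9% | 2.1% |
| 0.3 | 83% | 68% | 21% | 17.9% | 2.8% |
| 0.5 | 81% | 70% | 17% | 14.2% | 2.6% |
| 0.7 | 80% | 72% | 12% | 9.8% | 2.4% |
| 0.9 | 80% | 76% | 7% | 5.4% | 1.3% |
| 1.0 | 81% | 81% | 0% | 0% | 0% |

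A bivariate-normal calculation of the joint power gives 65%, 67%, 69%, 72% and 75% for phi 0 to 0.9, in agreement with the third column.

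**Only bothersomeness improves.** Bothersomeness 35% to 55%, ODI 35% in both arms. The VR-MBCT composite rate is 0.35·0.55 + phi·√(0.2275·0.2475), against the control composite rate above:
- phi 0: 12.3% versus 19.3%. Composite positive in about 27% of trials, two-test rule in about 2%.
- phi 0.5: 23.6% versus 31.1%. Composite positive in about 22%, two-test rule in about 2.5%.

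**Two data sets with 97 per arm, control versus VR-MBCT responders.**
- ODI 34 vs 53 (p=0.006), bothersomeness 34 vs 53 (p=0.006), both measures 24 vs 33 (p=0.16): two-test rule positive, composite negative.
- ODI 34 vs 47 (p=0.058), bothersomeness 34 vs 47 (p=0.058), both measures 20 vs 40 (p=0.002): two-test rule negative, composite positive.

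**The case against.** The strongest reply is that the decision rule is not in doubt. Sections 2.10 and 2.11 state the same rule, 2.11 specifies that "separate regression models will be fitted for functional disability and self-reported back pain bothersomeness", and nothing in the article tests a composite. A reader might infer from the conflicting definitions that the result which decides the trial has been left open, to be chosen once the data are in. The article does not support that: a team claiming success on the composite would break a published rule. This part of the objection stands.

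The composite wording can also be read as loose phrasing. Section 2.4 opens in the plural, the definition in 2.10 sits between two references to co-primary outcomes, and the Discussion sets no analysis. That is plausible for 2.10 and the Discussion. It does not rescue the last sentence of 2.4, which calls the endpoint a composite, requires concurrent improvement and presents this as the definition of treatment response, in the very section that defines the primary outcome.

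The size of the disagreement rests on an unstated correlation and on one of the two disputed readings of 35%/55%. It is also lopsided: in most discordant trials the stated two-test rule is the stricter one, so harm follows only if reporting departs from that rule. Both points are fair, which is why a range is shown. An analysis plan that is not shown cannot remove the conflict, because both forms are in this one article.

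**Conclusion.** The point holds as a contradiction between the endpoint definition and stated objective on one side and the planned analysis and success rule on the other. With 35% versus 55% on each endpoint and 97 per arm, the two verdicts differ in about 27% of trials at phi 0, falling to 7% at phi 0.9, mostly composite positive and two-test negative. If only bothersomeness improves, the composite is positive in about 22–27% of trials and the two-test rule in about 2–2.5% (phi 0 to 0.5). These figures depend on the assumed correlation, on equal rates for the two endpoints and on unadjusted tests; the contradiction depends on none of them.

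The power statement is affected too. If 35%/55% applies to each endpoint, 97 per group gives 80% power per endpoint but only about 65–76% for the rule that both be significant, over phi 0 to 0.9. The statement in 2.10 that power is adequate for both outcomes is then true only endpoint by endpoint.

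**What to change.** Before outcome data by group are seen (the Data Availability statement says collection is under way):

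- Align 2.4, the definition in 2.10 and the Discussion objective with the rule already in 2.11: two co-primary endpoints at week 8, at least 30% improvement in ODI and at least 30% improvement in bothersomeness, each tested at two-sided 0.05, with success only if both are significant.
- Remove the words composite and concurrent from 2.4.
- State in 2.10 that 35% and 55% apply to each endpoint.
- Restate the power in 2.10 as 80% per endpoint, with joint power of about 65–76% at 97 per group for phi 0 to 0.9.

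The cost is a wording amendment, with no new data item, and a less favourable stated power. The sponsor should see that before signing: on the same assumptions, 80% joint power would need 120 per group at phi 0.5 (120/0.9, rounded up to 134 per group, 268 in total) and 108 per group at phi 0.9 (240 in total). Keeping 214 is possible, but not with 80% claimed for the joint rule. Reporting the both-domains responder as a secondary outcome is optional and is not needed to resolve the conflict.
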